The target population for the HD-PPP programme include existing HA patients who fulfill the designated clinical criteria and are currently receiving HD in HA hospitals, new ESRD patients with contraindications for PD or patients who are currently on PD but are at risk of treatment failure. Eligible patients who choose to enroll in the programme will receive HD treatment in their selected community HD centre run by a private or charitable organization, and will pay no additional fees. The frequency of dialysis and other medical decisions would be overseen by the HA nephrologist looking after that particular patient. HD-PPP participants are followed up regularly at the renal specialist outpatient clinic (SOPC) to monitor their HD adequacy, renal function and other relevant clinical parameters.

As part of the development of a new health care service programme, it is important to include an evaluation component, best undertaken by an independent third party working in close collaboration with the programme planners, providers and administrators, to examine whether the programme delivers the care that it is intended to deliver, to the desired standard. The effectiveness of the programme in benefitting the health of service recipients and the sustainability of the programme can also be determined over a longer period of time. Such findings will provide valuable evidence to help those providing front-line care as well as those developing and coordinating the programme to improve the quality of patient care, and to support the continued funding and expansion of the programme.

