### Hypotheses

The following hypotheses will be tested:The criteria on structure and process should be achieved by all participating HA renal units and community HD centres;The dialysis for patients should be adequately maintained (Kt/V ≥ 1.2 for patients receiving 3 HD sessions per week or ≥ 1.8 for those receiving 2 HD sessions per week) after 12, 24, 36 and 48 months in the programme;Patients in the programme should report no worse outcomes as patients managed by usual care in the HA (control);

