### Subjects

All patients participating in the HD-PPP programme between 1 March 2010 and 30 June 2014 will be included in the evaluation on process of care. All HD-PPP participants and an equal number of non-HD-PPP participants (eligible for HD-PPP but not participating) matched by age and gender will be included in the evaluation on the outcomes of care. The non-HD-PPP subjects will be selected from the HA patient database by the HA Statistics and Workforce Planning Department. Subjects will be recruited via a letter from the HA or on-site by HKU research assistants upon enrolment in the HD-PPP programme.

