#### Evaluation on outcomes of care

Anonymized data on clinical parameters at baseline, 12, 24, 36, 48 and 60 months after enrollment will be retrieved from the CMS by the HA statistics team.

For patient-reported outcomes, HD-PPP subjects and non-HD-PPP subjects will be invited in person at the community centre/renal unit to complete a telephone/face-to-face survey on health-related quality of life at enrolment into the HD-PPP (or equivalent time for non-HD-PPP), and then again at 12, 24, 36, 48 and 60 months. The follow up surveys will also include questions assessing patient enablement and global rating of change in health condition. The trained research assistant administering the patient-reported outcomes questionnaire survey will also obtain written informed consent from each patient prior to commencing the survey.

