## Discussion

The HD-PPP is a novel programme which is increasing the availability of publically funded HD for needy ESRD patients. With 725 patients receiving HD in publically funded hospitals as of December 31, 2011 [18] and a cumulative total of 120 patients ever being enrolled in the HD-PPP as of March 31, 2012, the HD-PPP has already expanded the capacity for HD by roughly 17 %. There remains a waitlist for available vacancies supporting the popularity of this programme. This evaluation study will provide objective evidence to inform decisions about its continuation and further expansion and to encourage ongoing improvements.

Two similar programme evaluation studies on the Risk Assessment and Management Programme for diabetic [19] and for hypertensive patients [20] in primary care are currently underway in Hong Kong. These authors highlight a variety of issues encountered when doing action research including the importance of stakeholder collaboration and communication, regular feedback and planning meetings, data monitoring and protocol adherence, which are also applicable to our evaluation of the HD-PPP programme. Some of the specific observations, lessons learned and challenges encountered as we carry out the HD-PPP evaluation study are discussed below.

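### The control definition admits an unknown share of patients who are not on HD or who may later enrol, so the controlled comparison could partly reflect modality or crossover

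*Protocol article*

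**What the plan says.** All references are to the protocol article.

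- **Subjects.** The outcome evaluation includes all HD-PPP participants and as many controls, who are "eligible for HD-PPP but not participating" and are matched to participants on age and gender. The Hospital Authority (HA) statistics department selects the controls from its database. Inclusion runs from 1 March 2010 to 30 June 2014.
- **Background.** The programme's target population has three routes of entry. The first is "existing HA patients who fulfill the designated clinical criteria and are currently receiving HD in HA hospitals". The other two are "new ESRD patients with contraindications for PD or patients who are currently on PD but are at risk of treatment failure".
- **Hypotheses.** Adequacy is Kt/V of at least 1.2 on three HD sessions a week, or at least 1.8 on two. A separate hypothesis holds that programme patients report outcomes no worse than controls under HA usual care.
- **Outcome measures and Data analysis.** Dialysis adequacy and haemoglobin are clinical outcomes. Clinical outcomes are compared between participants and controls by independent t-test or chi-square test, and no adjustment is named.
- **Evaluation on outcomes of care.** The baseline survey is at programme enrolment, "or equivalent time for non-HD-PPP". Follow-up runs to 60 months.
- **Discussion.** "There remains a waitlist for available vacancies".

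**The concern.** A controlled evaluation of shared care should set community HD against hospital HD. The control rule does not secure that contrast. It borrows programme eligibility, and two of the three routes do not require the patient to be on HD. Matching on age and gender does nothing about modality.

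Three things are at stake:

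1. **Adequacy.** The thresholds depend on the number of HD sessions a week, so a control on PD or not yet dialysed has no threshold to be judged against.
2. **The no-worse hypothesis and haemoglobin.** Part of any difference could come from the controls' modality or stage of disease rather than from quality of care.
3. **Crossover.** An eligible patient on the waitlist is a control today and may be a participant later. Enrolment spans more than four years and follow-up reaches five, yet the text gives no rule for that patient.

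**Working it through.** **Step 1. Is there a design figure to reproduce?** No. The article gives no sample size, margin or expected control mix. The only related figure is the stated capacity gain of roughly 17%: 120 / 725 = 16.6%, which agrees.

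**Step 2. Read the control rule against eligibility.**

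| Route into the programme (Background) | On HD when eligible? | Meets the control rule if not enrolled? | Kt/V threshold in Hypotheses? |
|---|---|---|---|
| Hospital HD patient | Yes | Yes | Yes |
| New ESRD, PD contraindicated | Not necessarily | Yes | Only once on HD |
| On PD, at risk of failure | No | Yes | No |

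The usual-care label in Hypotheses does not narrow this, because the Background says HA policy puts PD first. No other text limits controls by modality or time on dialysis.

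**Step 3. Which analyses are touched?** The Kt/V hypothesis concerns patients in the programme against a fixed standard and needs no controls. The comparison with controls does need them, and so does the no-worse hypothesis.

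**Step 4. Illustration for adequacy.** All inputs here are assumptions: n = 120 per group (borrowed from cumulative enrolment at March 2012), two-sided alpha 0.05, the same true adequacy p among HD patients in both groups, all participants on HD, and a share s of controls not on HD who are counted as not adequate.

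- Control proportion: q = p(1 − s). False gap: p − q = p × s.
- Chance of a significant test: Φ[(gap − 1.96 × SE₀) / SE₁], with SE₀ = √(2 p̄(1 − p̄)/n), p̄ = (p + q)/2, and SE₁ = √((p(1 − p) + q(1 − q))/n).
- Worked case, p = 0.80 and s = 0.10: q = 0.72, gap = 0.08, SE₀ = 0.0551, SE₁ = 0.0549, chance = Φ(−0.51) ≈ 30%.

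| s | Gap, p = 80% | Chance | Gap, p = 90% | Chance | Controls left if dropped instead |
|---|---|---|---|---|---|
| 5% | 4.0 points | 11% | 4.5 points | 18% | 114 |
| 10% | 8.0 | 30% | 9.0 | 51% | 108 |
| 20% | 16.0 | 79% | 18.0 | 95% | 96 |
| 30% | 24.0 | 98% | 27.0 | over 99% | 84 |

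Dropping the unscorable controls avoids the false gap but breaks the matched sets.

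**Step 5. Crossover.** If a share c of controls joined early, took on the full programme effect and stayed in the control group, the contrast would shrink to 1 − c of its true size: 90%, 80% or 70% for c = 10%, 20% or 30%. For a no-worse claim, that pushes towards apparent equality. The size of the waitlist is not given, so c is assumed.

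**Step 6. Is an HD-only control pool plausible?** 725 / 120 = 6.0 hospital HD patients per participant, before the clinical criteria and matching are applied.

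**The case against.** The case against has real force on several points.

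- **The mix is unknown.** No figure shows that many controls are off HD. The aim speaks of HD patients and subjects are approached at a community centre or renal unit, so the database selection may in practice have returned HD patients only. This stands: the point is about what the rule permits.
- **The primary adequacy outcome.** A reader might infer that the primary Kt/V result is compromised. The documents do not support that, because the Kt/V hypothesis is for programme patients alone.
- **Direction of bias.** A reader might also infer that controls with failing PD would do worse and so flatter the programme. Participants enter by the same three routes, so no imbalance between groups is shown, and any deficit in such controls is an assumption. The Step 4 gaps further assume that unscorable controls are counted as failures, which the article does not state.
- **Selection on the future.** It is tempting to say that controls were chosen for never having joined by June 2014. The article describes no such procedure.
- **Time zero.** The baseline wording does loosely tie a control's start to the participant's enrolment. What it does not say is that the control must be on HD and eligible on that date.
- **Condensed article.** The full protocol may hold a tighter query. But the article states its selection rule outright, and that stated rule does not fit outcomes defined for HD only.

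**Conclusion.** The concern holds in limited form. As written, the control rule allows an unknown share of controls to be on PD or not yet dialysed, and the waitlist means some may later enrol. The between-group clinical comparison and the no-worse hypothesis could therefore partly reflect modality or crossover rather than quality of care. Adequacy cannot be scored for controls not on HD.

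The structure and process audit and the programme-only Kt/V hypothesis are untouched. The size and direction of any bias cannot be derived from the document. The gaps in Step 4 and the dilution in Step 5 show only how sensitive the comparison would be under the stated assumptions.

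**What to change.** For the controlled comparison:

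1. Require each control to be alive, receiving HD in an HA renal unit, eligible, and not yet in HD-PPP on the matched participant's enrolment date. That date becomes the control's baseline.
2. Match on, or adjust for, weekly HD sessions and time on HD. Restricting controls to HD is not enough alone, because participants may be new HD starters and would otherwise be set against long-established HD patients.
3. State in advance how controls who later join are analysed, and report both as-assigned and censored-at-joining results. Neither is free of problems: the first dilutes the contrast and the second may censor informatively.

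**Cost.** For clinical data this is a revised database query. Patient-reported baselines cannot be recreated, because Trial status says the third cycle is under way, so restrict that analysis to controls already surveyed who were on HD at baseline. Expect some unmatched participants or looser age matching, and fewer controls with patient-reported data. The ratio of 725 to 120 only suggests feasibility: the number meeting the clinical criteria and the enrolment at June 2014 are not given.

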### Data collection

#### Evaluation on structure and process

The programme coordinator of each participating HA renal unit and community HD service provider will be asked to complete a written structure of care questionnaire. For some questions respondents are also requested to submit evidence to support their response. Incomplete or equivocal responses are clarified by telephone and further confirmation and cross-validation is made during scheduled site-visits. Anonymized data will be retrieved from the computerized medical record system (CMS) by the HA statistics team to determine the process of care indicators including dropout rate, attendance at hospitals or community HD centres, compliance with follow up monitoring as per protocol etc.

#### Evaluation on outcomes of care

Anonymized data on clinical parameters at baseline, 12, 24, 36, 48 and 60 months after enrollment will be retrieved from the CMS by the HA statistics team.

For patient-reported outcomes, HD-PPP subjects and non-HD-PPP subjects will be invited in person at the community centre/renal unit to complete a telephone/face-to-face survey on health-related quality of life at enrolment into the HD-PPP (or equivalent time for non-HD-PPP), and then again at 12, 24, 36, 48 and 60 months. The follow up surveys will also include questions assessing patient enablement and global rating of change in health condition. The trained research assistant administering the patient-reported outcomes questionnaire survey will also obtain written informed consent from each patient prior to commencing the survey.

### Three evaluation and feedback cycles

Three evaluation (audit) cycles will be conducted with each having a specific focus. The first evaluation cycle tries to identify discrepancies between intended targets and actual practice in which may require changes in the structure and process of care. The second evaluation cycle is to determine the standards that are achievable after the HD-PPP programme has been established. The third evaluation cycle aims to assess the sustainability of the standards of care, and to document the impact of the HD-PPP programme. Each evaluation cycle involves an initial planning meeting to agree on the criteria for evaluation and the target standards, site visits by the research team to observe the programme in action, to cross-validate structural and process elements and to clarify areas of confusion, the collection and analysis of preliminary data, and a feedback meeting with programme coordinators and administrators to discuss findings, identify areas for quality enhancement and revise the evaluation framework as necessary. The evidence generated by the study serves as an impetus for changes to be made to the programme.

### Outcome measures

#### Primary

The proportion of centres that have satisfied each pre-set structure criterionThe proportion of patients who have complied with the process of careThe proportion of patients who have adequate HD measured by the Kt/V

#### Secondary

Clinical outcomes include dialysis adequacy and blood haemoglobin.Patient reported outcomes (PRO) are measured by the change in Short Form-12 version 2 (SF-12v2) scores, the Patient Enablement Instrument (PEI) and Global Rating Scale (GRS) scores at baseline and after 12 months.

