### Study instruments

There are four study instruments are used in this study, one to evaluate the structure of care and three to evaluate the PRO (Kidney Disease Quality of Life (KDQOL-36), the PEI and the GRS). Evaluation of the process and outcomes of care do not involve the use of study instruments as the necessary data are retrieved from the HA computerized medical record system by the Statistics and Workforce Planning Department.

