#### The Patient Enablement Instrument (PEI)

PEI will be used to measure patient’s enablement in coping with the illness and life [14]. It has 6 items and each rated on a 3-point scale (0 = the same or less; 1 = slightly improved/increased; 2 = greatly improved/increased). The summation of the item scores gives the PEI score with a higher score indicating better enablement. The PEI has been translated into Chinese and shown to be valid and reliable in the general Chinese population [15].

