#### The Global Rating Scale (GRS)

GRS, adapted from studies [16, 17], will be used to assess the subject’s global perception of any change in their overall health condition on a 7-point scale (−3 = much worse to 3 = much improved, with 0 = no change) over the past 12 months.

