### Data analysis

Descriptive statistics on standard of care will be calculated including the percentage of centres meeting each structure criterion, percentage of subjects enrolled, dropped out, receiving criterion process including HD, and percentage of subjects achieving each outcome criterion.The difference in clinical and PRO of patients who take part in the HD-PPP programme at baseline, 12, 24, 36 and 48 months will be compared by paired sample t-tests.Independent sample t-test or chi-square test as appropriate will be used to compare the clinical outcomes between HD-PPP participants and control patients.Independent sample t-test or chi square test as appropriate will be used to compare the clinical outcomes between results achieved in different evaluation cycles.

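### PEI and GRS are given a baseline and a paired analysis, but they are scheduled only in the follow-up surveys and already measure change

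*Protocol article*

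**What the plan says.** All references are to the protocol article.

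- **Outcome measures, Secondary.** The sentence opens "Patient reported outcomes (PRO) are measured by the change in Short Form-12 version 2 (SF-12v2) scores" and goes on to "the Patient Enablement Instrument (PEI) and Global Rating Scale (GRS) scores at baseline and after 12 months".
- **Evaluation on outcomes of care.** Both groups are invited to a "survey on health-related quality of life at enrolment into the HD-PPP (or equivalent time for non-HD-PPP" patients), repeated at 12, 24, 36, 48 and 60 months. The section then adds: "The follow up surveys will also include questions assessing patient enablement and global rating of change in health condition".
- **Study instruments.** PEI and GRS count as patient-reported outcomes: the article lists "three to evaluate the PRO (Kidney Disease Quality of Life (KDQOL-36), the PEI and the GRS").
- **PEI.** There are six items, "each rated on a 3-point scale (0 = the same or less; 1 = slightly improved/increased; 2 = greatly improved/increased"), which are summed.
- **GRS.** It records the patient's "global perception of any change in their overall health condition on a 7-point scale", from −3 to 3 with 0 as no change, looking back 12 months.
- **Data analysis.** Clinical and patient-reported outcomes of programme patients "at baseline, 12, 24, 36 and 48 months will be compared by paired sample t-tests". The two independent-sample comparisons that follow, with controls and between evaluation cycles, name clinical outcomes only.
- **Hypotheses.** The third states that programme patients should report outcomes no worse than those of usual-care controls.

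**The concern.** The outcome definition asks for a baseline PEI and GRS, and the analysis plan pairs patient-reported outcomes across a set of visits that includes baseline. The data collection section schedules neither scale at enrolment. An analyst who follows the text has no first member of the pair.

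The scales themselves make this more than a missing visit. Each asks the patient how things have changed, so the follow-up score is itself the change. Subtracting one such score from another answers a different question from whether patients improved.

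At stake is how two secondary outcomes are reported. The analyst would have to choose a substitute after the data are in. The readiest one, pairing two follow-up visits, can show no effect in patients who report benefit every year. Meanwhile the comparison that suits these scales and bears on the third hypothesis, programme against control at the same follow-up, is not among the stated analyses.

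**Working it through.** No sample size, power or error rate is involved. The check sets the sections side by side and then applies the paired difference to the scales.

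**Step 1: is there a baseline value to pair?**

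| Measure | Baseline wanted (Secondary outcomes) | Enrolment survey (Evaluation on outcomes of care) | Follow-up surveys |
|---|---|---|---|
| SF-12 (within KDQOL-36) | yes | yes, as quality of life | yes |
| PEI | yes | not scheduled | yes |
| GRS | yes | not scheduled | yes |

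A difference of 12 months minus baseline can be formed for SF-12. For PEI and GRS the baseline term is absent from the schedule.

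**Step 2: does the grammar rescue the outcome?** The phrase about change may govern all three measures or SF-12v2 alone. On the first reading, PEI and GRS need a baseline to form a difference. On the second, they are still scores to be reported at baseline. Both readings need a value that is not scheduled.

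**Step 3: what do the scores express?** The PEI total runs from 6 × 0 = 0 to 6 × 2 = 12, and every item is graded by degree of improvement, with no change and decline sharing the value 0. GRS runs from −3 to 3 and rates change over the preceding 12 months. Both are therefore already relative to an earlier state. A GRS taken at enrolment would describe the year before the programme.

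**Step 4: what would pairing two follow-ups give?** Let d = GRS at 24 months − GRS at 12 months.

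- Improved in both years: d = 2 − 2 = 0.
- Unchanged in both years: d = 0 − 0 = 0.
- Worsened in both years: d = (−2) − (−2) = 0.

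Three opposite courses give the same difference. PEI behaves likewise: the maximum at both visits gives 12 − 12 = 0.

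**Step 5: is there another stated test?** Data analysis names three inferential comparisons. Only the paired one mentions patient-reported outcomes; the other two are confined to clinical outcomes, which the Secondary section lists separately. The one inferential test stated for PEI and GRS is thus the one that their schedule and scale do not fit.

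**The case against.** The strongest reply is that this is loose drafting. Change may refer to SF-12v2 alone, in which case no PEI or GRS difference is prescribed and only a stray mention of baseline is wrong. Data analysis lists five time points without naming the pairs, so the 12-versus-24-month example shows what could happen, not what is planned. The article nowhere says outright that PEI and GRS are omitted at enrolment. An enrolment GRS would also not be meaningless: comparing the year before entry with the first programme year is an interpretable contrast. And PEI's status as a change scale is inferred from its response labels, since the article gives no reference period for it.

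These points limit the finding but do not remove it. Either reading of the sentence calls for a baseline value. A contrast between years before and after entry would need an enrolment administration that is not scheduled, and it would still compare two rates of change.

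A reader might infer two stronger conclusions, and the article supports neither:

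- *That the secondary patient-reported outcome as a whole cannot be computed.* The SF-12v2 change can be, and PEI and GRS at 12 months are scheduled.
- *That the kidney-specific KDQOL-36 subscales feed no outcome, or that naming SF-12v2 conflicts with KDQOL-36.* The article names KDQOL-36 as a patient-reported instrument, describes SF-12 as its generic core and tests patient-reported outcomes without restriction. The outcome indicators are in an additional file that is not shown.

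**Conclusion.** The point holds for PEI and GRS: two of the three patient-reported measures named in the secondary outcomes are given a baseline that the schedule does not provide, and a paired analysis that does not suit scales of change. No numerical bias can be attached to this. The zero difference for a patient at +2 twice illustrates the mechanism and is not an estimate of its effect in this study.

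The conclusion rests on two inferences. The first is that questions described as added in the follow-up surveys are not asked at enrolment. The second is that PEI's response labels make it a measure of change; for GRS the article says so directly. Severity is moderate: the three primary outcomes are untouched, and follow-up PEI and GRS remain usable once their analysis is restated.

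**What to change.** In **Outcome measures, Secondary**, separate the two kinds of measure. Suggested wording: *Patient-reported outcomes are (a) change from enrolment in SF-12v2 scores and (b) PEI and GRS scores at 12 months and at each later follow-up; PEI and GRS have no baseline value.*

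In **Data analysis**:

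- Restrict the paired tests on patient-reported outcomes to SF-12/KDQOL-36 scores.
- Add a comparison of PEI and GRS between HD-PPP and control patients at follow-up. Both groups are surveyed, and this serves the third hypothesis. The choice of method can be left to the SAP.
- Within HD-PPP, describe GRS against 0, its no-change value. The same does not suit PEI, whose lowest score is 0 and merges no change with decline.

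The cost is wording in two sections. No new instrument, visit or patient is needed, because the follow-up scores are already scheduled. Since Trial status reports that collection is ongoing, the change is best made before these scores are analysed.
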